**Table 1: Patient characteristics**

| **Characteristic** |
| --- |
|  |
| **Demographics** |
| Age |
| Female |
| Race |
| Region |
| **Year of cohort entry** |
| **Baseline lung disease** |
| Moderate COPD exacerbations |
| Severe COPD exacerbations |
| Total COPD exacerbations (moderate or severe) |
| SABA fills |
| SAMA fills |
| SAMA-SABA fills |
| Pneumonia hospitalizations |
| Respiratory antibiotic fills^b^ |
| Prior diagnosis of asthma (all available data) |
| Claim for home oxygen or oxygen equipment |
| CPAP/BiPAP |
| Spirometry |
| Index prescription by pulmonologist |
| Smoking |
| Pulmonary rehabilitation |
| LAMA |
| LABA |
| ICS |
| LAMA-LABA |
| ICS-LAMA-LABA |
| Chronic azithromycin |
| Roflumilast |
| Chronic prednisone |
| **Events within 30 days of cohort entry** |
| Moderate or severe COPD exacerbations |
| Respiratory antibiotic fill^b^ |
| **Other co-morbidities** |
| Combined comorbidity index |
| Frailty score |
| Obstructive sleep apnea |
| Hypertension |
| Diabetes |
| Obesity |
| Coronary artery disease |
| Peripheral vascular disease |
| Venous thromboembolic disease (DVT or PE) |
| Congestive heart failure |
| GERD |
| Renal failure |
| Osteoporosis |
| Dementia/other neurologic disease |
| Malignancy, non-metastatic |
| Metastatic solid organ malignancy |
| Anxiety disorder |
| Depression |
| **Healthcare utilization in baseline period** |
| Emergency department visits |
| Hospitalizations |
| 90-day readmissions |
| Office visits |
| Pulmonologist visits |
| Prescription drug claims |
| BMP or CMP |
| CBC with differential ordered |
| Electrocardiogram |
| Echocardiogram |
| CT scan |
| Bronchoscopy |
| Colonoscopy |
| Mammography |
| Bone-mineral density scan |
| Influenza vaccination |
| **Non-pulmonary medications** |
| Statins |
| Beta-blockers |
| ACE-inhibitors |
| ARBs |
| Calcium channel blockers |
| Thiazide-like and thiazide-type diuretics |
| Loop diuretics |
| Proton-pump inhibitors |
| H2-receptor blockers |
| Metformin |
| Sulfonylureas |
| SGLT2 inhibitors |
| DPP-4 inhibitors |
| GLP-1 receptor agonists |
| Benzodiazepines |
| SSRIs or SNRIs |

a. Our method for identifying respiratory antibiotics is described in Appendix Table 4, “Method for identifying respiratory antibiotics.

1. Outcome variable and study follow-up
   1. Outcome variables and study follow-up:

**Primary effectiveness outcome:** First moderate or severe COPD exacerbation

Moderate COPD exacerbations are defined as requiring prednisone for 5-14 days, and severe COPD exacerbations are defined as requiring hospitalization (with COPD in the primary position). The full codes for moderate exacerbations, severe exacerbations, and moderate or severe exacerbations are below. Defining moderate exacerbations based on prednisone fills (of 5-14 days) has been validated with PPV of 0.73 (0.70-0.77).^3^ Note that, on sensitivity analysis, we will require both a prednisone and an antibiotic fill (PPV 0.80 [95% CI 0.74-0.86]).^3^ Defining severe COPD exacerbations based on COPD diagnosis codes in the primary position has been validated with a PPV of 0.86.^4^

The primary analysis is time to first moderate or severe COPD exacerbation. In secondary analyses (see below), we will analyze cumulative exacerbations during one year of follow up using a Prenctice, Williams, and Peterson Total Time Model. We will require that distinct episodes of exacerbation be separated by at least 14 days. Therefore, if a patient meets the criteria for an exacerbation more than once within 14 days, this will be counted as 1 unique episode that begins at the first exacerbation within the episode.

Episodes that meet both moderate and severe exacerbation criteria within 14 days of each other will be counted as 1 severe exacerbation that begins at the time of meeting the criteria for the first exacerbation within the episode, regardless of whether the criteria are for a moderate or severe exacerbation.

Therefore, there are 2 types of prednisone fills that would otherwise meet criteria for moderate exacerbations but are instead grouped as severe COPD exacerbations: (1) First, prednisone fills that occurred within 14 days AFTER the end of a COPD hospitalization will count as a severe COPD exacerbation beginning with the start of the COPD hospitalization. The prednisone script is likely just completing the therapy that was begun in the hospital and so should not count as a new exacerbation. (2) Second, prednisone scripts that occurred within 14 days BEFORE the start of a COPD hospitalization will count as a severe COPD exacerbation beginning with the start of the prednisone script. When prednisone is not enough and hospitalization is required, this episode is a severe exacerbation.

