**Part 1: Background**

Fluticasone-salmeterol has long been approved for the treatment of chronic obstructive pulmonary disease (COPD). In the US, GlaxoSmithKline markets two different inhalers containing fluticasone-salmeterol: Advair Diskus (first approved in 2000) and Advair HFA (first approved in 2006). The former, a dry powder inhaler, is approved for the indications of both COPD and asthma, while the latter, a metered-dose inhaler, is only approved for the indication of asthma. However, a small randomized controlled trial showed that Advair HFA had similar efficacy to Advair Diskus when treating COPD.^1^ Yet, metered dose inhalers have also been associated with more errors than dry powder inhalers.

Given ongoing clinical uncertainty, we will analyze the comparative effectiveness and safety of fluticasone-salmeterol delivered via metered-dose inhaler (Advair HFA) vs dry powder inhaler (Advair Diskus) among patients with COPD treated in routine clinical practice. The primary effectiveness outcome will be first moderate or severe COPD exacerbation; the primary safety outcome will be first pneumonia hospitalization. Secondary outcomes will include the annual rate of total moderate or severe COPD exacerbations (analyzed separately and together), first moderate exacerbation, first severe exacerbation, and annual rate of total pneumonia hospitalizations.

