**6.1 Cohort Summary**

All patients with COPD, defined by 3 outpatient claims or 1 inpatient claim in the prior 3 years (PPV 0.82 [0.72-0.89]),^2^ who initiated a prescription for fluticasone-salmeterol (Advair HFA) (exposure) vs. fluticasone-salmeterol (Advair Diskus) (referent) between January 1, 2007 and November 30, 2023. We will require a 180-day washout period for both the exposure and the referent. We will also require 180 days of continuous insurance coverage prior to cohort entry. We will include patients who received other therapy in the baseline period (whether single-agent inhalers [ICS, LAMA, LABA], LAMA-LABAs, or triple therapy). In other words, we will include patients who may be stepping up therapy (from monotherapy), stepping down therapy (triple therapy), or switching (from LAMA-LABA). Following other studies, we will exclude patients who are less than age 40 to increase the specificity of COPD diagnoses. This will help further ensure that patients entering the cohort are receiving triple therapy for COPD rather than another respiratory condition.

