The baseline covariate assessment period for all measures will start 180 days before cohort entry and will stretch up to and include the day of cohort entry with the following exceptions: (1) We will assess age, sex, race, region, year of cohort entry, and index prescription by a pulmonologist only on the day of cohort entry; (2) We will assess the presence of any prior asthma diagnosis using all available data and stretching up to (and including) the day of cohort entry. Diagnosis based covariates will be defined using any care setting and any diagnosis position unless otherwise specified. All codes for these variables are provided in Appendix Table 3, “Covariates.” The variable names are as listed below in Table 1. All variables listed below will be included in our propensity score model. We will use a missing indicator in our propensity score model in the case that data are missing for any covariates.

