| **3** | Prior diagnosis of asthma | GOLD guidelines recommend ICS-containing regimens for those with a prior diagnosis of asthma. This subgroup analysis seeks to examine the comparative effectiveness of Advair Diskus and HFA in this population where ICS-based regimens are thought to be particularly beneficial. | Addresses comparative effectiveness and safety in lower risk subgroup | None |
| **4** | Excluding patients with recent asthma diagnosis codes (in prior 3 years). | GOLD guidelines recommend ICS-containing regimens for those with a prior diagnosis of asthma. This subgroup analysis seeks to examine the comparative effectiveness of Advair Diskus and HFA in this population where ICS-based regimens are thought to be particularly beneficial. | Addresses comparative effectiveness and safety in lower risk subgroup | Low power |
| **6** | Spirometry before cohort entry | Maintenance inhalers are more likely to be effective for patients who have a proven diagnosis of COPD (as measured by spirometry). We want to examine whether, among patients with spirometry (i.e. patients most likely to benefit from inhaler therapy), there is any difference between Advair Diskus and HFA. | Addresses comparative effectiveness and safety in population enriched for COPD (closer to RCT population) | We do not know the actual measurements from the spirometry. |
| **7** | Index-prescription from a pulmonologist | Pulmonologists may be more likely to assign guideline-recommended therapy compared to other practitioners. We will examine whether Advair HFA has similar effectiveness to Advair Diskus among patients whose index prescription is from a pulmonologist. | Addresses generic quality in population enriched for patients who should be receiving guideline-concordant care. | Low power. |
| 8 | Cohort entry between 2007-2018 | This is the primary time during which Advair Diskus and Advair HFA were on the market without generic competition, limiting confounding from competing devices that patients might be alternatively prescribed. | Limits confounding from competing inhalers, providing a more direct comparison of Advair Diskus vs. HFA. | None. |

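### Recent or active asthma may stay imbalanced in the primary analysis, because the propensity score holds asthma only as an ever/never flag plus non-specific proxies

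*Protocol*

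**What the plan says.** **Indication.** The Protocol's Background says Diskus is approved for both COPD and asthma. Of HFA it says: "while the latter, a metered-dose inhaler, is only approved for the indication of asthma".

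**Adjustment.** The Covariates section says of Table 1: "All variables listed below will be included in our propensity score model". Table 1 has one asthma line, "Prior diagnosis of asthma (all available data"). The section defines it so: "We will assess the presence of any prior asthma diagnosis using all available data". It is the only diagnosis covariate exempted from the 180-day window. Section 6.1 sets the minimum history: "We will also require 180 days of continuous insurance coverage prior to cohort entry".

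**Outcome.** Section 8 states: "Moderate COPD exacerbations are defined as requiring prednisone for 5-14 days". Section 8.1.A builds this from prednisone fills, removes those close to a COPD hospitalization, and asks for no diagnosis code. The severe component needs COPD as the primary diagnosis of an admission.

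**Other places where asthma appears.** Subgroup row 3 splits on prior asthma. Row 4 is "Excluding patients with recent asthma diagnosis codes (in prior 3 years"). The footnote to the subgroup table adds the complement of each subgroup. Sensitivity row 10 is high-dimensional propensity score (hdPS) matching.

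**The concern.** By the protocol's own account, asthma is the labelled difference between the two devices, so it is a plausible reason to choose HFA over Diskus. It can also produce the outcome: an asthma attack treated with a short prednisone course meets the moderate-exacerbation definition. A variable linked to both device choice and outcome needs to be measured as it stands at cohort entry.

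The flag does not do that. A patient with one asthma code many years ago and a patient with asthma claims last month get the same value. A patient with only 180 days of enrolment can be flagged only on recent claims, while one with long enrolment can be flagged on old ones. Weighting equalises the flag between arms. It need not equalise current asthma among flagged patients.

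At stake is the Aim 1 hazard ratio. The comparison is of two devices delivering the same drugs, so the true difference may be small, and a shift of a few percent in one direction would affect interpretation. A larger cohort would not remove it.

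**Working it through.** **Stated figures.** The protocol gives no sample size, event count, asthma prevalence or asthma distribution by arm, and the balance summary is a figure that is not shown. There is nothing to reproduce. The validation figure for the prednisone definition ("has been validated with PPV of 0.73 (0.70-0.77")) implies that 1 − 0.73 = 27% of such events were not confirmed, but the protocol does not say how many of those were asthma.

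**Step 1: what balancing the flag leaves open.** Assume the ever-asthma flag is perfectly balanced. Let pE be the share of the cohort with the flag, a1 and a0 the active-asthma shares among flagged HFA and Diskus starters, and RR the event-rate ratio for active versus inactive asthma that remains after the other covariates. Approximately,

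B = (1 + pE·a1·(RR − 1)) / (1 + pE·a0·(RR − 1)).

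Diskus is the referent, so B above 1 counts against HFA. All inputs are assumptions: a0 = 0.5, a1 = 0.6 to 0.8, pE = 0.3 or 0.5, and pE = 1 for the prior-asthma stratum of row 3.

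| RR | Overall, pE = 0.3 | Overall, pE = 0.5 | Row 3 stratum, pE = 1 |
| --- | --- | --- | --- |
| 1.1 | 1.003–1.009 | 1.005–1.015 | 1.010–1.029 |
| 1.25 | 1.007–1.022 | 1.012–1.035 | 1.022–1.067 |
| 1.5 | 1.014–1.042 | 1.022–1.067 | 1.040–1.120 |
| 2.0 | 1.026–1.078 | 1.040–1.120 | 1.067–1.200 |

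Example: pE = 0.5, a1 = 0.8, RR = 2.0 gives (1 + 0.40)/(1 + 0.25) = 1.12. In the row 3 stratum, a1 = 0.6 and RR = 1.1 gives 1.06/1.05 = 1.010. If a1 = a0, B is exactly 1.

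**Step 2: how far proxies might help.** One simulated cohort of 400,000 assumed:
- 40% ever-asthma, of whom 55% active;
- log-odds of HFA raised by 0.6 for active asthma and 0.1 for the flag;
- with active asthma, mean SABA fills of 1.8 instead of 0.8, mean prednisone fills of 0.50 instead of 0.25, and ICS use of 20% instead of 10%.

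The standardized mean difference for active asthma was:
- unweighted: 0.297;
- logistic weighting on the flag alone: 0.135 (weighted shares 0.270 and 0.213);
- flag plus SABA fills, prednisone count and ICS: 0.116 (0.264 and 0.214).

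The three proxies removed (0.135 − 0.116)/0.135 = 14% of what the flag left. The remaining bias factor was 1.012 at RR 1.25 and 1.041 at RR 2.0. The real score holds more proxies, of unknown strength, and uses CBPS rather than plain logistic weighting. This shows only that proxies can leave imbalance behind.

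**The case against.** **Table 1 is not blind to current airway disease.** If an asthma flare looks like a prednisone fill, a baseline flare is already counted among baseline moderate exacerbations and, if recent, among the 30-day events. SABA fills, ICS, chronic prednisone, emergency visits and pulmonologist visits are also in the score. A reader might infer that nothing in the 180-day baseline reflects active asthma, and that would be wrong. What remains is that none of these terms is specific to asthma; each also tracks COPD severity.

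**The plan has other checks.** Row 4 removes patients with asthma codes in the prior 3 years, and its complement gives recent asthma its own stratum. hdPS matching is an alternative overall analysis with many empirical covariates. One might infer that the overall comparison is never examined under different confounding control; it is. But the subgroups leave the primary estimate as it was, and a different hdPS result could not be attributed to asthma. Row 3's asthma stratum still mixes remote and current disease.

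**Device choice.** It is tempting to call asthma the main driver. The protocol gives approved indications, not prescribers' reasons, and every patient has claims-defined COPD and is at least 40. Channelling is plausible, not shown.

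**Outcome.** The prednisone fill is one of two components; the severe one needs a primary COPD code. That dilutes the effect. The three alternative moderate definitions in sensitivity row 5 do not help, because none of them asks for a COPD diagnosis.

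**Conclusion.** The point holds as a risk of residual confounding in the primary Aim 1 estimate. The protocol fixes a covariate list in which the diagnosis that separates the two labels has no measure of recency or activity, although the plan defines a recent-asthma window elsewhere. If active asthma is channelled to HFA and raises prednisone use beyond what the proxies capture, the bias runs against HFA.

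The size is unknown. On the assumed inputs it ranges from negligible (1.003) to 1.12 overall, and it is larger in the prior-asthma stratum. The low end is the more relevant one if the baseline proxies absorb most of the excess risk, since only the residual rate ratio counts.

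Two stronger readings are not supported. A reader might conclude that active asthma is in fact imbalanced after weighting; no distribution by arm is given, so this cannot be known. A reader might also set the bias against the expected width of the confidence interval; no sample size or event count is given to allow that. This is a worthwhile improvement to the primary model and does not invalidate the design.

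**What to change.** Keep the ever-asthma flag and add two terms to Table 1 and the CBPS model:
- any asthma diagnosis in the prior 3 years, as already defined for subgroup row 4;
- asthma-coded claims or visits in the 180-day baseline. Because 180 days of enrolment is required, this is the one asthma measure observed over the same window in every patient.

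Report balance on both terms overall and in the prior-asthma stratum of row 3. In row 4 both terms are zero by construction. In its complement the 3-year term is constant and only the 180-day measure can vary, so only that one is informative there.

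The cost is deriving one new claims variable, re-fitting the weights and repeating the balance comparison in the Statistical analysis section, with a possible small loss of effective sample size. None of this needs outcome data.

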| **4** | Exclude the first 30 and 60 days after cohort entry. | Patients may receive ICS-LABAs when their symptoms are bad (but before a true moderate or severe COPD exacerbation). We will assess whether any differences between Advair Diskus and Advair HFA exist when we exclude these early exacerbations. | This allows us to focus on the long-term effectiveness of these maintenance therapies. | Follow-up time will be low because patients discontinue their inhalers so frequently. We may not have sufficient power to detect small treatment effects in this analysis. |
| **5** | Alter the definition of a moderate exacerbation: (a) require an office or ED visit before the prednisone fill; (b) require both prednisone (5-14 days) and a respiratory antibiotic; (c) count either a prednisone script (5-14 days) or a respiratory antibiotic script | This will allow us to assess the robustness of the results to variations of the outcome definition. | Each of these outcome definitions has been employed elsewhere in the literature. | (a) We will exclude many patients who have moderate COPD exacerbations but do not come into clinic. (b) We will exclude many patients who are having moderate exacerbations (antibiotics + steroids are only recommended for patients meeting specific criteria such as purulent sputum); (c) We will include patients who receive antibiotics for reasons having nothing to do with COPD exacerbations |
| **6** | Alter the definition of a severe exacerbation: allow for a COPD diagnosis in any position for the hospitalization | This will allow us to assess the robustness of the results to variations of the outcome definition. | The outcome definition in the primary effectiveness analysis may exclude patients who are having a COPD exacerbation but are admitted for a different primary reason (e.g. MI). | This is a less specific definition than the one we employed since many patients will have a code for COPD during a hospitalization even though they are not having an exacerbation. |

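### Table 1's 30-day block pools prednisone-treated with hospitalized exacerbations and has no row for other recent admissions, so discharge shortly before cohort entry is balanced only in part

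*Protocol*

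**What the plan says.** Under Covariates, the Protocol sets a default assessment window of 180 days up to and including cohort entry. It states that every variable in Table 1 enters the propensity score. Under Statistical analysis, the covariate balancing propensity score (CBPS) model is a logistic model on those same variables.

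The block headed "Events within 30 days of cohort entry" has two rows: "Moderate or severe COPD exacerbations", as a single combined item, and a respiratory antibiotic fill. The lung-disease block lists "Severe COPD exacerbations" separately from moderate ones, and also "Pneumonia hospitalizations". The utilization block lists hospitalizations, 90-day readmissions and emergency department visits. These carry no 30-day label, so the 180-day default applies.

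The outcome section separates the two kinds of exacerbation: a moderate one is identified by a 5-14 day prednisone course, a severe one by an admission with COPD as the primary diagnosis.

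Three planned secondary analyses bear on the point. Sensitivity row 4 excludes the first 30 and 60 days after entry, sensitivity row 10 uses high-dimensional propensity score matching, and subgroup 2 with its footnote analyses separately the patients with no baseline COPD hospitalization.

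**The concern.** A patient who starts the inhaler days after leaving hospital and one who starts after a prednisone course at home are plausibly at different short-term risk of exacerbation and pneumonia. The Protocol keeps these states apart when it defines outcomes: "prednisone fills that occurred within 14 days AFTER the end of a COPD hospitalization" are folded into the severe episode and not counted as new moderate ones. In the 30-day baseline block the two get the same value. A recent admission for pneumonia, heart failure or anything else without COPD in primary position has no 30-day row of its own. That matters most for the primary safety outcome, which is itself a pneumonia hospitalization.

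Early events carry weight in this design. On-treatment follow-up is capped at one year, and the Protocol says of its early-exclusion analysis, "Follow-up time will be low because patients discontinue their inhalers so frequently". If one device is started near discharge more often than the other, weights that balance only 180-day counts can leave part of that difference in place. Balance diagnostics confined to the listed rows would not report it.

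**Working it through.** The Protocol gives no figure for discharge timing, so there is nothing of its own to reproduce. The check has two parts.

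**1. Can the listed rows separate recent from remote admission?** This assumes that the baseline rows follow the section 8.1 definitions and that the 30-day block looks back from entry.

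| Row | Patient A: prednisone at day -100, COPD admission at day -10 | Patient B: COPD admission at day -100, prednisone at day -10 |
|---|---|---|
| Moderate, 180 days | 1 | 1 |
| Severe, 180 days | 1 | 1 |
| Total, 180 days | 2 | 2 |
| Moderate or severe, 30 days | 1 | 1 |
| Hospitalizations, 180 days | 1 | 1 |

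These rows cannot tell A from B. In the same way, a non-COPD admission at day -10 and one at day -150 give the same hospitalization count. The separation works in one case: for a patient whose only exacerbation was a COPD admission, the severe count and the 30-day flag together identify it as recent. A main-effects model does not force balance on that combination.

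**2. How much could remain?** All inputs here are assumptions. In a simulation of 400,000 patients:

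- Event rates in the last 30 days were 2.5 times those in earlier 30-day windows.
- About 7.4% of patients had a discharge in the last 30 days.
- The HFA share was about 18% among the rest (intercept -1.5).
- Device choice depended on recent discharge only.
- Weights were stabilized inverse-probability weights from a plain logistic model (not CBPS) on four rows: moderate count, severe count, pooled 30-day flag and all-cause hospitalization count.

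With p1 and p0 the weighted shares recently discharged on HFA and Diskus, and RR the outcome ratio for recent discharge:

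bias factor = [1 + p1(RR - 1)] / [1 + p0(RR - 1)]

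| Device odds ratio | Crude shares, HFA / Diskus | Weighted shares | SMD, crude to weighted | Factor, RR 2 | RR 2.5 | RR 3 |
|---|---|---|---|---|---|---|
| 0.67 | 0.0545 / 0.0782 | 0.0612 / 0.0765 | -0.091 to -0.059 | 0.986 | 0.979 | 0.973 |
| 1.0 | 0.0724 / 0.0743 | 0.0730 / 0.0742 | -0.007 to -0.005 | 0.999 | 0.998 | 0.998 |
| 1.5 | 0.0993 / 0.0682 | 0.0875 / 0.0705 | 0.119 to 0.065 | 1.016 | 1.023 | 1.030 |
| 2.0 | 0.1188 / 0.0625 | 0.0963 / 0.0665 | 0.216 to 0.114 | 1.028 | 1.041 | 1.053 |

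For example, at odds ratio 1.5 and RR 2 the factor is 1.0875 / 1.0705 = 1.016. At odds ratio 2.0 and RR 3 it is (1 + 2 × 0.0963) / (1 + 2 × 0.0665) = 1.1926 / 1.1330 = 1.053.

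Share of the crude difference removed by the existing rows:

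- Odds ratio 0.67: 1 - 0.0153/0.0237 = 35%
- Odds ratio 1.5: 1 - 0.0170/0.0311 = 45%
- Odds ratio 2.0: 1 - 0.0298/0.0563 = 47%

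Adding one row for any discharge in the last 30 days brought the SMD to 0.00 and the factor to 1.00.

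A second simulation (600,000 patients, 7% recently discharged, post-discharge hazard about 2.5 times the reference) weighted on the 180-day hospitalization count and the 30-day exacerbation flag. At device odds ratios 1.3 / 1.5 / 2.0, the difference in shares went from 0.017 / 0.031 / 0.058 crude to 0.011 / 0.020 / 0.036 weighted. The hazard ratio bias was 0.8% / 1.6% / 2.8%. That is smaller than the formula gives at RR 2.5, so the range should be read as approximate.

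Pooling taken alone (400,000 patients; 6.9% severe and 15.9% moderate in the last 30 days; device odds 1.5 / 2 / 3 after a severe event) left SMDs of 0.04 to 0.08 and hazard ratio bias of 0.9% / 1.2% / 1.8%.

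**The case against.** The strongest reply is that recent discharge is far from ignored. Severe exacerbations, pneumonia admissions, all-cause hospitalizations, readmissions and emergency visits all enter the model, as do many correlates such as 30-day antibiotics, oxygen, heart failure and frailty. The simulations used only two or four rows, so they probably overstate what the full model would leave. Most residual SMDs fall below 0.1, the mark the Protocol uses when counting imbalanced higher-order terms. Every input is assumed, and at a device odds ratio of 1.0 there is no material imbalance.

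All of that stands, and it rules out several stronger readings:

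- A reader might infer that starting at discharge is simply unbalanced between devices. The 180-day rows balance it in part.
- A reader might infer that a patient discharged after a non-COPD admission registers nothing in the 30-day block. One who fills a qualifying prednisone course or a respiratory antibiotic would score there.
- A reader might infer that one device is started at discharge more often. The Protocol says nothing on this in either direction.
- A reader might infer that the 180-day total row is redundant and should go. That cannot be confirmed without Appendix Table 3, and an exactly redundant row does no harm.

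The planned secondary analyses help but leave the primary estimate as it is. Row 4 removes early events and does not balance the patients. High-dimensional matching may or may not select a recency variable. In patients with no baseline COPD hospitalization the pooling problem disappears, on the section 8.1 definitions, but the missing row for other admissions does not.

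**Conclusion.** The point holds in a limited form. A hospital discharge in the 30 days before entry is not separately targeted by the primary weights and is balanced only in part. If device choice depends on recent discharge given the other Table 1 rows, both primary hazard ratios could carry residual confounding of unknown direction. Its size is roughly 1-3% with about 7% recently discharged, device odds ratios of 1.3 to 2.0 and outcome ratios of 2 to 2.5. The simple formula reaches 4.1% at the top corner of that range, and about 5% at odds ratio 2.0 with outcome ratio 3. No figure here comes from the Protocol.

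The reading also assumes that no 30-day admission rows are defined in Appendix Table 3 or the design diagram, neither of which is at hand. This is a cheap improvement in covariate choice for a design that already tries to capture acuity at entry. It does not show that the plan is wrong or that the result will be biased.

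**What to change.** In Table 1, replace the pooled 30-day exacerbation row with two rows, moderate and severe, and add a row for any hospital discharge in [-30, 0]. Include all three in the CBPS model and report their weighted standardized mean differences with the other balance results. The 180-day rows can stay as they are.

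The data come from claims already read for the 180-day rows. The cost is re-estimating the weights and repeating the comparison of balancing methods under Statistical analysis, since CBPS was chosen on its performance in this dataset. A slight change in effective sample size is possible.
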